#### *Aim 4 Comparative Effectiveness Analyses*

##### *Aim 4 Analyses*

We will use standard step wedge analytic methods (see citations in reference list for PASS report). We will use repeated measures Poisson models to compare control vs LHS intervention conditions on the response rate ratio for the SU cascade outcomes and the opioid related outcomes. The Poisson or zero-inflated Poisson regression models will be performed using SAS GENMOD to fit repeated measures generalized linear models (GLIM) with generalized estimating equations (GEE) to account for the fact that event data for youth will be measured repeatedly over time and to account for the correlation due to within-organization clustering. The outcome data will be entered into the model as event counts for every 6-month period of the 36 months of implementation (6 months of control condition for all clusters, then 30 months of intervention), reported separately for each arrest record. Multiple arrests for the same youth will be used in the model. In the power analysis (described below), we conservatively based the power calculations on the number of unique youth arrested. The actual analysis will use a random effect to incorporate data from youth who have multiple arrests.

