The amount of time (in days) exposed to the implementation for each adolescent arrestee will be accounted for in the rate ratio by defining the "offset" variable as the natural log of the number of days of exposure for every 6-month period of implementation. The primary denominator will be the number of arrested youth in the rolling intake cohort (e.g., % referred as a percentage of the number in the arrestee intake cohort). For some outcomes, another separate outcome will be derived and analyzed using a smaller denominator (e.g., % referred as a percentage of YJJ in need of treatment). The denominator for % in need (i.e., % screened positive) will be YJJ screened. The denominator for the % engaged will be the YJJ initiated. Because some youth will have multiple arrests, they could also have multiple screenings. In addition, for a single arrest and single screening, there could be multiple referral events over any 6-month period; for a single referral, there could be multiple treatment initiation events; and for a single treatment initiation, there could be multiple occurrences of an engaged event (i.e., 2+ behavioral health visits within 30 days after initiation) over any 6-month period. Therefore, the model will capture these multiple events as counts for every 6-month period.

Covariate-by-6-Month-Period interactions will be tested to determine whether the outcome response rates changed differently over time for different values of covariates.

In addition, youth-level covariates (demographics and health visit data) will also be included as predictors.

In the next step of the model, we will include organizational-level (i.e., county-by-system [JJ and CMHC]) survey predictors including staff characteristics (JPO age, sex, and race/ethnicity, time in current position, highest/type degree, number of previous positions, salary, caseload size, job (dis)satisfaction rating, turnover intentions, and burnout rating), implementation variables (readiness,

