However, we acknowledge some youth will be placed out of the home (DOC and residential placement). Additionally, some youth will migrate out of the community (which will be assessed by address data from state-wide databases; INPC, Medicaid, & DCS). Thus, we conservatively estimate that roughly 70% of 2,170 (i.e., 1,519) adolescent arrestees per year will be available in-home in the community from the 8 counties (4,557 total over 36 months of implementation which includes 30 months of intervention plus 6 prior months in which all cohorts experience the control condition under the baseline period). Based on an annual 30% recidivism rate, we estimate that 30% (1,367) of the projected 4,557 arrests for this trial will represent repeated arrests from the same youth, yielding an estimated 3,190 unique youth available in the administrative data over the 36 months of the primary outcome measurement period. We will actually collect and use administrative data for 5 years (not just 6 months) prior to the start of intervention; however, to be conservative, the step wedge power calculation assumed only 6 months of prior baseline administrative data (i.e., 36 months of primary administrative measurement). Additionally, although all data (including multiple arrests for the same youth) will be used in the model, to be conservative for the power analysis, we assumed that the maximum sample size available for the power calculations is the number of unique youth (3,190).

Our design has 8 counties (i.e., clusters). A projected maximum available sample size of 3,190 unique youth, over the 36-month primary evaluation period, yields: (1) 531 youth per 6-month time period, (2) an average of 398 maximum youth per cluster over 36 months (*M* in the Step Wedge Design), and (3) an average of 66 youth per cluster per 6-month time period (*m* in Step Wedge design).

We used the PASS software to calculate power for a test of two poisson rates (control condition event rate vs treatment condition event rate) in a cluster-randomized step wedge design. Our step wedge design is an "incomplete design" in which a different number of clusters (i.e., counties) start the intervention at each step. Given 8 clusters and practical considerations, we decided to initiate intervention for 3 clusters in cohort 1, then in the next step another 3 clusters in cohort 2, and then in the next step another 2 clusters in cohort 3.

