For the PASS input parameters, we assumed an intra-class (i.e., intra-cluster) correlation coefficient of 0.01, a two-sided test of the rate ratio (intervention vs control conditions), and an alpha of 0.05. We calculated power for 4 different hypothesized poisson rate ratios (effect size) ranging from 1.25 to 1.40 by .05. Results show that a total sample size of 2,400 youth (i.e., average of 300 unique youth per cluster with an average of 50 youth per cluster per 6-month time period) will provide 80% to 99% power for detecting population rate ratios, for various outcomes derived from administrative data described elsewhere, ranging from 1.25 to 1.40 (See PASS Report below). Thus, the available total sample size of 3,190 unique youth (i.e., average of 398 unique youth per cluster with an average of 66 youth per cluster per 6-month time period) will provide more than ample power (e.g., exceeding 80% power for a rate ratio of 1.25). In addition, the actual analysis will include youth with multiple arrests which will increase power further.

#### PASS Results Report for Power for Comparing Poisson Rates for Aim 4

Design Type: Incomplete (Custom)

Test Statistic: Wald Z-Test

Hypotheses:  $H_0: \lambda_1/\lambda_2 = 1$  vs.  $H_1: \lambda_1/\lambda_2 \neq 1$

|       | Design | Clusters | Cluster Size | Sample Size | Trt Rate    | Ctrl Rate   | Ratio | ICC   | Alpha |
|-------|--------|----------|--------------|-------------|-------------|-------------|-------|-------|-------|
| Power | S/T/R  | K        | M/m          | N           | $\lambda_1$ | $\lambda_2$ | RR1   |       |       |
| 0.80  | 5/6/1  | 8        | 300/50       | 2400        | 1.25        | 1.00        | 1.25  | 0.010 | 0.050 |
| 0.91  | 5/6/1  | 8        | 300/50       | 2400        | 1.30        | 1.00        | 1.30  | 0.010 | 0.050 |
| 0.97  | 5/6/1  | 8        | 300/50       | 2400        | 1.35        | 1.00        | 1.35  | 0.010 | 0.050 |
| 0.99  | 5/6/1  | 8        | 300/50       | 2400        | 1.40        | 1.00        | 1.40  | 0.010 | 0.050 |

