### Summary Statements

A sample of 8 clusters in an incomplete (or custom) stepped-wedge cluster-randomized design with 6 time periods (including the baseline), 5 steps, and an average of 300 subjects per cluster with an average of 50 subjects per cluster per time period (for a total sample size of 2400 subjects) achieves 80% power to detect a ratio of 1.25. The treatment event rate is assumed to be 1.25 under the alternative hypothesis. The control event rate is 1.00. The test statistic used is the two-sided Wald Z-Test. The ICC is 0.010, and the significance level of the test is 0.050.

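### Aim 4 commits to GEE with 8 randomised counties and is powered on a Wald Z test, with no small-sample method stated; error rate and power both depend on that

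*Protocol*

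**What the plan says.** Protocol, Aim 4 Analyses: Poisson or zero-inflated Poisson models are to be "performed using SAS GENMOD to fit repeated measures generalized linear models (GLIM) with generalized estimating equations (GEE"), in part "to account for the correlation due to within-organization clustering". The same paragraph adds, for repeat arrests: "The actual analysis will use a random effect to incorporate data from youth who have multiple arrests". It names no variance estimator, test statistic or reference distribution.

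Protocol, Aim 4 Power: "Our design has 8 counties (i.e., clusters"). The roll-out is to "initiate intervention for 3 clusters in cohort 1, then in the next step another 3 clusters in cohort 2", then the last 2 in cohort 3. The power inputs include an intra-cluster correlation of 0.01 and "a two-sided test of the rate ratio (intervention vs control conditions), and an alpha of 0.05". The Summary Statements of the Aim 4 PASS report say: "The test statistic used is the two-sided Wald Z-Test". Stated power with 8 clusters, 6 periods and 50 youth per county per period (N = 2,400) is 0.80, 0.91, 0.97 and 0.99 for rate ratios 1.25, 1.30, 1.35 and 1.40.

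A later modelling step in Aim 4 Analyses adds "organizational-level (i.e., county-by-system [JJ and CMHC]) survey predictors", with implementation and fidelity measures entered as time-varying.

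No small-sample correction, t reference or permutation test appears anywhere in the protocol.

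**The concern.** The county is the randomised unit, so there are 8 independent clusters. Six period effects and one LHS term make 7 parameters estimated from them. The sandwich variance used with GEE is justified when clusters are many. With 8 it is biased downward, and a normal reference ignores its imprecision. The Cascade and opioid-related outcomes, both listed as primary, are tested with this model, so a test that rejects too often would bear directly on the main effectiveness conclusion. The power calculation uses the same normal reference, so the trial may have less power than stated even if the analysis is later corrected.

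The model is also not uniquely specified. GEE is a marginal method with a working correlation. A random effect belongs to a different, conditional model and cannot be part of a GEE fit.

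**Working it through.** **1. Reproducing the stated power.** Inputs from Aim 4 Power: the 8 x 6 design matrix (rows with 5, 5, 5, 4, 4, 4, 3, 3 intervention periods; columns with 0, 3, 6, 8, 8, 8 counties on intervention), m = 50, ICC 0.01, rates 1.25 and 1.00.

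Hussey-Hughes variance: Var = I s2 (s2 + T t2) / [(I U - W) s2 + (U^2 + I T U - T W - I V) t2], where s2 is the variance of a county-period mean and t2 the between-county variance.

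- I = 8, T = 6; U = 33 (sum of the matrix); W = 9 + 36 + 3 x 64 = 237; V = 3 x 25 + 3 x 16 + 2 x 9 = 141.
- I U - W = 264 - 237 = 27. U^2 + I T U - T W - I V = 1,089 + 1,584 - 1,422 - 1,128 = 123.
- Total variance is taken as the mean of the two rates, 1.125. So t2 = 0.01 x 1.125 = 0.01125 and s2 = 0.99 x 1.125 / 50 = 0.022275.
- Var = 8 x 0.022275 x (0.022275 + 6 x 0.01125) / (27 x 0.022275 + 123 x 0.01125) = 0.01600 / 1.98518 = 0.00806; SE = 0.0898.
- Difference / SE = 0.25 / 0.0898 = 2.785. Power with Z = Phi(2.785 - 1.960) = 0.795, against the stated 0.80.

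The other ratios give 0.911, 0.968 and 0.991, against 0.91, 0.97 and 0.99. The inputs are therefore understood correctly. Other variance choices fit less well at ratio 1.25: control-rate variance 0.84, treatment-rate variance 0.75, log scale about 0.70.

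**2. Changing only the reference distribution.** With the same standard error and t on 6 degrees of freedom (8 counties minus 2, a conventional choice), power is 64%, 79%, 89% and 95% for the four ratios.

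**3. Type I error by simulation.** The null is no LHS effect. Poisson counts were generated by county and period, with a county effect matching the ICC (with and without county-by-period variation). Event rates were 1.00 (the protocol's) and 0.3 (an assumption). The fitted model has period effects and an LHS indicator, clustered on county. Unequal counties use the Aim 4 Power referral table (40 to 706 a year), scaled to 2,170 x 0.49 / 2 = 532 youth per period, that is about 3,190 in all. Rejection rates at nominal 5%:

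| Variance and reference | Equal counties | Protocol county sizes |
|---|---|---|
| Uncorrected sandwich, Z, ICC 0.01 | 15-17% | 17-22% |
| Uncorrected sandwich, Z, ICC 0.05 (independence working correlation) | 16-17% | 22-24% |
| Exchangeable model-based SE, Z, ICC 0.01 | about 5-8% | about 5-9% |
| Mancl-DeRouen sandwich, t(6) | 3-5% | 2-4% |

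The last row covers both ICCs and, at ICC 0.01, runs with the longer baseline described below. Monte Carlo standard error is about 0.8-0.9 points at 2,000 runs and 1.3-1.4 points at 800 runs for the sandwich-Z rates. A separately programmed repeat of the first row gave 16.6% and 21.7%. Adding nine earlier control periods, to mimic the five-year baseline, left the sandwich-Z rate at 15-19%, because the number of clusters stays at 8.

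**4. Power at ratio 1.25 with tests that hold their level.** A permutation test (type I error 4.7-5.3%) had power 0.69 with 2,400 youth in equal counties, 0.83 with 3,190 in equal counties, and 0.75 with 3,190 in the protocol's county sizes. Mancl-DeRouen with t(6) gave about 40-55% with 2,400, depending on the working correlation (54% at the upper end, exchangeable). Only step 2 isolates the Z reference. The simulated figures also reflect a log-scale model and the working weights.

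**5. Later-step predictors.** 11 staff characteristics + 4 implementation variables + 5 fidelity variables = 20, against 8 x 2 = 16 county-by-system organisations.

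**The case against.** The strongest reply is that the Wald Z test is named only for the power calculation. Aim 4 Analyses does not say which variance or reference distribution the GEE test will use, and a statistical analysis plan not shown here could add a correction. That stands. A reader might infer that the protocol prescribes Wald Z tests for the analysis, or that false positives will occur three to four times too often. The document supports neither. The inflation applies if the usual uncorrected sandwich is used with Z; an exchangeable model-based standard error shows much less. What the reply does not rescue is the power, which is stated in the protocol and tied to Z.

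A reader might also infer that county clustering could be ignored in favour of youth. The text disfavours that, since it says within-organisation correlation will be accounted for.

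Nor should the 20 predictors be read as damaging the main comparison. They are county-by-system rather than county-level, partly time-varying, and enter after the control-versus-LHS comparison. Joint entry of all 20 is a plausible reading but is not stated. The mix of GEE and a random effect is a wording inconsistency confined to repeat arrests, though it leaves the primary model undefined.

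**Conclusion.** The point holds in conditional form. The protocol commits its effectiveness comparison to GEE with 8 randomised counties, states no small-sample method, and sizes the comparison on a normal reference. With an uncorrected county-clustered sandwich and Z, type I error is about 15-17% (equal counties) to 17-22% (the protocol's county sizes) at nominal 5%. The stated 80% power at ratio 1.25 with 2,400 youth becomes about 64% when only the reference changes to t(6), and was below 80% at that sample size for every level-preserving test tried. At 3,190 youth the permutation test exceeds 80% only if counties are equal in size, which the protocol's own table shows they are not.

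These figures rest on ICC 0.01 (0.05 as a check), log-normal or gamma county effects, Poisson counts and the 3/3/2 roll-out. They are simulation results, not figures from the protocol. The permutation figures also assume unrestricted assignment. The predictor overload is a separate, lesser point.

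**What to change.** - Name county as the cluster for the LHS effect.
- Choose either GEE or a random-effects model, and delete the other from Aim 4 Analyses.
- Base p-values and intervals for the LHS effect on one of: a permutation test over the allocations the actual randomisation allowed; a small-sample-corrected variance (such as Mancl-DeRouen) with a t reference; or a county random-effects Poisson model, with a youth effect for repeat arrests if wanted, and small-sample degrees of freedom. If the 3/3/2 assignment was unrestricted there are 8! / (3! 3! 2!) = 40,320 / 72 = 560 allocations. The protocol does not say whether it was, so this must be confirmed.
- Restate the Aim 4 power for the chosen test, using the county sizes in the referral table.
- Label the organisational predictors exploratory and enter them one per model.

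The cost is revised text, a short program and a new power calculation, with no change to trial conduct. The real price is a materially lower stated power: least with the permutation test among the alternatives quantified here, most with Mancl-DeRouen and t(6). Power for the random-effects option was not calculated.

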**AIM 4:** *Assess the impact of ADAPT.* Conduct a stepped wedge cluster randomized controlled trial to assess the impact of LHS alliances on the Cascade for YJJ. We will analyze administrative data linked across JJ and health systems to assess the long-term, community-wide effects of ADAPT on public health and safety outcomes (e.g., lower rates of SU-related outcomes and criminal recidivism).

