### *LHS Alliances by Site*

LHS alliance teams will be composed of existing JDAI local data teams. The local JDAI data teams consist of JJ personnel and community members. The goals of the data teams are to assess local data to determine youth risk level and to improve outcomes among YJJ. LHS alliance teams will utilize these teams, along with additional team members from the local CMHC, to conduct continuous quality improvement cycles.

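### Aim 4 rates are divided by arrested youth, a group that LHS itself may change, so a per-arrestee ratio can move without any change in care and cannot on its own support a community-wide claim.

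*Protocol*

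**What the plan says.** Protocol, Aim 4 Analyses, sets the denominators:

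- Main one: "The primary denominator will be the number of arrested youth in the rolling intake cohort".
- Certain outcomes get a second version on a narrower base, such as referral among youth who need treatment.
- Share in need: "The denominator for % in need (i.e., % screened positive) will be YJJ screened".
- Engagement is taken over those who have started treatment.

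The model is a Poisson GEE on six-month event counts, with log days of exposure as offset. It is named for the Cascade and opioid outcomes. Counts are entered for each arrest record, and "Multiple arrests for the same youth will be used in the model".

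Elsewhere in the protocol:

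- Eligibility Criteria: a youth enters the administrative sample by being arrested or otherwise referred to juvenile justice in a participating county, before or during the study period.
- Potential Benefits: reducing recidivism is one of the things the intervention is designed to do. Outcome Measures lists recidivism as Primary.
- Aim 4 Power: 30% of the projected 4,557 arrests (1,367) are taken to be repeats.
- LHS Alliances by Site: the alliances are built on existing county data teams that include justice personnel. "The goals of the data teams are to assess local data to determine youth risk level and to improve outcomes among YJJ".
- Synopsis, Aim 4: the trial is to assess "long-term, community-wide effects of ADAPT on public health and safety outcomes".

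**The concern.** Counties are randomised, but the youth who form the denominator are identified afterwards, by justice events. At least one of those events, rearrest, is something LHS is meant to change. The cohort counted after a county starts may therefore differ in size or make-up from the cohort counted before, because of the intervention. A ratio per arrestee then mixes two things: what happens to a given youth, and who is counted.

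Period effects do not separate them, because the shift begins at each county's own start date, as the treatment effect does. The planned demographic and health-visit covariates may absorb part of a change in mix. Control for corrections and residential placement deals with time away from the community, not with entry to the cohort.

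At stake is how the Aim 4 result is read. Losing low-risk youth raises Cascade rates, which looks like benefit, and raises opioid events per arrestee, which looks like harm. Drawing in more low-risk youth does the reverse. A community-wide effect cannot be read from a rate whose base is the arrested group.

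**Working it through.** **Inputs from the protocol.** 8 counties starting in groups of 3, 3 and 2; 6 periods; 50 youth per county-period in the power table (66 expected); ICC 0.01; two-sided alpha 0.05; control rate 1.00; 2,170 arrests/referrals a year; 30% repeats; about one third of youth with a substance use disorder (Synopsis). The share of intake lost (f) and the event rate of the lost youth relative to the cohort mean (r) are assumptions.

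**Step 1: the plan's own figures.** 2,170 × 0.70 = 1,519 a year; × 3 = 4,557; × 0.70 = 3,190 youth. For power, the Hussey–Hughes variance on the 8 × 6 design matrix is

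Var = Kσ²(σ² + Tτ²) / [(KU − W)σ² + (U² + KTU − TW − KV)τ²],

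with U = 33, W = 237 and V = 141, so the two brackets are 27 and 123. At a ratio of 1.25, with Poisson variance at the mean of the two rates, σ² = 1.125/50 = 0.0225 and τ² = (0.01/0.99) × 1.125 = 0.01136. Then Var = 0.00814, SE = 0.0902, z = 0.25/0.0902 = 2.77, and power = Φ(2.77 − 1.96) = 0.79. Setting τ² = 0.01 × 1.125 and σ² = 0.99 × 1.125/50 gives 0.795. The plan states 0.80, so it reproduces; so do 0.91, 0.97 and 0.99 for ratios 1.30, 1.35 and 1.40.

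**Step 2: apparent ratio with no true effect.** If a share f of intake is no longer recorded once LHS starts, events fall to 1 − rf and the denominator to 1 − f:

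apparent ratio R = (1 − rf)/(1 − f), so f = (R − 1)/(R − r).

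| Relative rate r of lost youth | f giving R = 1.25 | R at f = 10% |
|---|---|---|
| 0 | 0.25/1.25 = 20% | 1.11 |
| 0.25 | 0.25/1.00 = 25% | 1.08 |
| 0.5 | 0.25/0.75 = 33% | 1.06 |
| 0.75 | 0.25/0.50 = 50% | 1.03 |
| 1 (proportional) | none | 1.00 |

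The 20% case means 0.20 × 2,170 = 434 youth a year, or 0.20/(2/3) = 30% of those without a disorder. In the other direction, adding 25% event-free youth gives 1/1.25 = 0.80, enough to cancel a true 1.25.

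**Step 3: smaller shifts.** A 9% event-free loss gives 1/0.909 = 1.10. Under the variance in Step 1, with numbers per county-period held fixed, SE = 0.0872 at 50 youth, so z = 0.10/0.0872 = 1.15 and the test rejects about 21% of the time. At 66 youth it rejects about 26%. The nominal rate is 5%.

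**Step 4: simulation.** Poisson stepped-wedge data were simulated at 66 youth per county-period and fitted with county and period effects (medians of 200 runs).

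| f, r | Per arrestee | Fixed denominator |
|---|---|---|
| 0, 0 | 1.00 | 1.00 |
| 20%, 0 | 1.26 | 1.00 (1.005) |
| 33%, 0.5 | 1.24 (1.235) | 0.82 |
| 20%, 1 | 1.00 | 0.80 |

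The last two rows show that counts on a fixed denominator also move with intake, so neither analysis is sufficient alone.

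**Step 5: the repeat-arrest route.** If the effective denominator counts arrest records, halving repeats removes 0.5 × 30% = 15% of it. With events unchanged the ratio is 1/0.85 = 1.18. If the lost records take their events with them, the shift is smaller and vanishes when the loss is proportional.

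**The case against.** A reader might infer that every Aim 4 rate is divided by all arrestees, and that a change in diversion practice should be expected to reproduce 1.25 by itself. The documents do not support that.

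- The share in need is taken over youth screened, engagement over youth who initiated, and one version of referral over youth in need. Losing low-need youth leaves referral among those in need unmoved and engagement largely so.
- The protocol nowhere says that LHS will change arrest, diversion or referral into the system, or that the alliance agencies control it. The data teams already exist, so their reform role does not begin with LHS. Diversion after a recorded referral removes nobody from the sample.
- The Poisson models are not named for rearrest, and no denominator is given for recidivism.
- The denominator sentence speaks of arrested youth, and a youth rearrested less often stays in it. The 1.18 therefore holds only if records are the unit and events do not fall with them.
- Reaching 1.25 takes a large and selective loss.
- Aim 4 also asks about the Cascade among justice-involved youth, for which a rate among those youth is the natural measure. Intake checks may sit in the SAP, which was not available here.

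All of this stands and limits the point to a conditional risk. It does not remove it. All the named denominators are nested in a cohort formed after randomisation, the intended effect on recidivism can alter that cohort, and the protocol itself sets the community-wide aim beside a denominator that cannot deliver it.

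**Conclusion.** The point holds as a conditional risk of post-randomisation selection, worth correcting but not fatal to the design. The apparent ratio with no true effect ranges from 1.00 (proportional loss) through 1.10 (9% event-free loss) to 1.25 (20% event-free loss, or 33% at half the mean rate). These sizes rest on assumed values of f and r and ignore whatever the planned covariates would absorb. The documents do not support the stronger inference that such a shift will happen, or that all Aim 4 rates are equally exposed. What is firm is that the stated denominators cannot separate a change in care from a change in who is counted, and that they do not measure a community-wide effect.

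**What to change.** Keep the arrestee denominator and add two pre-specified supportive analyses, or cross-refer to the SAP if it already has them:

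1. The LHS effect on the number of arrests/referrals per county-period, first and repeat separately, with case mix by condition. The records are already being collected, including five pre-study years.
2. For opioid outcomes, recidivism and Cascade events: county-period counts of youth with the event, with county and period effects and log resident youth population as offset.

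Report both beside the per-arrestee ratio. State in advance that a per-arrestee change may reflect selection if analysis 1 shows that intake volume or mix changed. Base community-wide statements on analysis 2.

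Agreement of the counts should not be a pass/fail rule. A true per-youth gain of 1.25 with a proportional 20% fall in arrests gives a count ratio of 1.25 × 0.80 = 1.00, so a real benefit would be dismissed.

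The cost is a few extra models and public population figures, whose size the documents do not give. Analysis 2 will be noisier, with 8 counties and one at 40 referrals a year.

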*Substance use care cascade.* A primary outcome of interest is the SU care cascade (Cascade). The Cascade includes a spectrum of outcomes. At any point in the Cascade, a young person can “drop out.” The earliest stage of the Cascade occurs within the juvenile justice system: identification of treatment need (i.e., screening and assessment) and referral to services. The latter end of the Cascade occurs within the CMHC: treatment initiation, engagement, and completion. We are interested in determining whether the LHS intervention is effective in improving the Cascade. We will evaluate this outcome utilizing administrative data on the entire population of YJJ across all 8 sites. We will gather Cascade data from the local CMHCs as well as Department of Child Services (DCS) and Medicaid. The reason for gathering data from DCS and Medicaid is they both provide funds for outpatient services. Thus, if a young person receives substance use services outside of the local CMHC, we will be able to gather at least a portion of it from these data sources. We may find that the effectiveness of LHS is improved for young people seeking services outside of the CMHC. With that said, we have collaborated with the largest CMHC of each jurisdiction and most jurisdictions only have one CMHC located in their county. We will also be able to control for time spent outside of the community by controlling for commitments to Department of Corrections (gathered from the juvenile justice data set) and residential placement (gathered from DCS and Medicaid).

*Criminal recidivism.* We will also assess whether the LHS intervention is effective in limiting recidivism. We will utilize the existing juvenile justice information system to assess recidivism. We will focus on the prediction of new criminal charges rather than charges associated with previous criminal behavior (e.g., technical violation, probation violation and warrants).

*Opioid-related outcomes.* By linking with data collected through the Regenstrief Institute Addictions Data Commons, we will be able to assess a variety of outcomes. This includes hospital and Emergency Department visits for opioid use disorders (OUD) as well as emergency medical service runs due to opioid use. These data elements are now incorporated within the Addiction Data Commons.

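### Cascade outcomes are labelled as percentages of youth but modelled as repeat event counts, and the engaged event contradicts its own definition

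*Protocol*

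**What the plan says.** The Cascade is one of the primary outcomes in the protocol's Outcome Measures table. Under Assessing Outcomes it is described as a series of stages, and the text says "At any point in the Cascade, a young person can" drop out. That is a statement about whether a person gets to the next stage.

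Aim 4 Analyses expresses the outcomes as percentages with people in the denominator. The primary denominator is arrested youth. The alternatives are youth in need of treatment, youth screened (for the percentage in need) and youth who initiated (for the percentage engaged). The numerators are different. One screening may give several referrals, one referral several initiations, and "for a single treatment initiation, there could be multiple occurrences of an engaged event (i.e., 2+ behavioral health visits within 30 days after initiation"). The conclusion drawn is "Therefore, the model will capture these multiple events as counts for every 6-month period". Counts are kept separately for each arrest record, and the offset is the log of days of exposure. The text gives no first-event rule, no cap and no once-per-youth or once-per-arrest version.

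**The concern.** A percentage of youth reaching a stage and a rate of events at that stage are different quantities. Aim 4 asks the first question: are more young people identified, referred, started and kept in treatment? The model as written answers the second. It cannot tell a county that refers more youth from one that refers the same youth more often.

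The engaged outcome has a separate defect. One initiation has one 30-day window after it, and the words two or more already absorb further visits. The stated definition and the stated possibility of several occurrences cannot both be applied. An analyst would have to improvise, for example with rolling windows or pairs of visits, and each choice gives a different count.

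This is a rule that the protocol fixes, not a detail left to a later plan.

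**Working it through.** **Inputs (protocol, Aim 4 Power and its PASS Summary Statements).** Eight clusters in six 6-month periods, starting 3, 3 and 2 at a time; 50 youth per cluster-period (66 projected as available). "we assumed an intra-class (i.e., intra-cluster) correlation coefficient of 0.01"; "The test statistic used is the two-sided Wald Z-Test"; "the significance level of the test is 0.050"; "The control event rate is 1.00". The design "achieves 80% power to detect a ratio of 1.25". Projected arrests are 4,557, from 3,190 unique youth.

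**Step 1: reproduce the stated power.** The Hussey-Hughes variance of the treatment effect is

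Var = I·s²·(s² + T·t²) / [(I·U − W)·s² + (U² + I·T·U − T·W − I·V)·t²].

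The printed design matrix gives I = 8, T = 6, U = 33, W = 237, V = 141. Hence I·U − W = 27, and U² + I·T·U − T·W − I·V = 1089 + 1584 − 1422 − 1128 = 123.

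At ratio 1.25 the mean Poisson variance is (1.00 + 1.25)/2 = 1.125. So s² = 1.125/50 = 0.0225 and t² = (0.01/0.99) × 1.125 = 0.01136. Then Var = 0.00814, SE = 0.0902, and power = Φ(0.25/0.0902 − 1.96) = 0.79.

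For ratios 1.25, 1.30, 1.35 and 1.40 the results are 0.79, 0.91, 0.97 and 0.99, against 0.80, 0.91, 0.97 and 0.99 in the protocol. The stated power follows from its own inputs.

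**Step 2: what the count model estimates.** Events per youth = (share of youth reaching the stage) × (events per youth reaching it). Take an assumed share referred of 40% in both conditions.

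- Referrals per referred youth 1.00 under control and 1.25 under intervention: 0.40 × 1.25 / (0.40 × 1.00) = 1.25. The ratio of youth referred is 0.40/0.40 = 1.00.
- The share cancels, so the result is the same at 20% or 60%.
- In the other direction, 1.25 under control and 1.00 under intervention gives 0.80, again with no change in youth referred.

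**Step 3: the quantity is not a percentage.** 4,557 / 3,190 = 1.43 arrests per youth. One referral per arrest over unique youth would read as 143% referred.

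**Step 4: power for a 0/1 outcome.** A control rate of 1.00 cannot be a proportion that rises by 25%, so the stated power does not cover a reached/not-reached outcome. The same formula applies with variance p̄(1 − p̄) for the 0/1 outcome, or p̄ for a Poisson count with the same control mean, where p̄ averages the two conditions. The ratio is 1.25 and the control proportions are assumed, because the protocol gives none.

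| Control proportion (assumed) | 0/1, 50 per cluster-period | 0/1, 66 per cluster-period | Poisson count, same mean, 50 |
|---|---|---|---|
| 20% | 0.29 | 0.36 | 0.24 |
| 30% | 0.46 | 0.57 | 0.33 |
| 40% | 0.66 | 0.77 | 0.42 |
| 50% | 0.84 | 0.92 | 0.50 |

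At the same control mean the 0/1 outcome has more power than the count. The shortfall against 80% comes from assuming one event per youth per unit time, not from scoring each stage once.

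**The case against.** **Counts are an open choice.** The protocol declares a Poisson rate ratio with an exposure offset, explains that events recur, and sizes the trial on that basis. A rate may exceed 1. This stands in part: counts suit recurrent events such as overdose visits. It does not rescue a numerator of events over a denominator of people that is then called a percentage of youth.

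**The model handles repeats.** The offset adjusts for exposure time, and the GEE and random effect adjust for correlation. None of them removes repeat events from the point estimate.

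**Repeats may be balanced.** This stands. The ratio is distorted only if repeats per youth differ between conditions. A reader might infer that quarterly review of Cascade data under the intervention prompts re-referral of youth who did not attend, and so inflates the effect. The protocol does not say so: it describes linked local data and tables for committee meetings. The opposite is also possible, since better first hand-offs would need fewer re-referrals.

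Large illustrative figures depend on the same inference. With 50 youth referred and 30 not initiating, re-referring all 30 under intervention and none under control gives 80/50 = 1.60. If half of the control non-initiators are also re-referred, it is 80/65 = 1.23. All of these inputs are assumed.

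**Scope is limited.** Referral is one stage of one of five primary outcomes. Extra referrals without extra initiations would show as a flat initiation result. The engaged definition, taken literally, already limits the count to one per initiation, so that contradiction may change little numerically.

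**Conclusion.** The point holds as a mismatch between the named outcome and the modelled one, together with a contradictory engaged definition. Under the stated rule, a 25% difference between conditions in events per youth reaching a stage, in either direction, is enough to move the ratio to 1.25 or 0.80 with no change in the youth reached. That follows from the arithmetic whatever the share. Whether such a difference will arise, how large it would be and which way it would go are unknown. The documents do not support a claim that the intervention causes it or that the trial is biased towards benefit.

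The printed power is correct for a control rate of 1.00 but says nothing about once-only outcomes. The power figures given here rest on assumed control proportions and on the protocol's ICC of 0.01. This should be fixed before analysis, but it does not invalidate the design.

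**What to change.** In Aim 4 Analyses:

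- Make the primary Cascade measure a 0/1 outcome per arrest record for each stage: screened, positive, referred, initiated, engaged. Use arrests as the matching denominator, so that numerator and denominator share a unit, and keep the handling of clustering by youth and county.
- For these outcomes, drop the log-days offset or replace it with a fixed follow-up window. Assign each outcome to the period of the arrest, so that an arrest under control with later initiation under intervention has a defined place.
- Keep event counts as a secondary service-volume rate.
- Delete the statement that one initiation can yield several engaged events.

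The records needed are the same. There are two costs. Repeat events earn no credit in the primary measure. Aim 4 power must be recalculated with a stated control proportion for each stage, and it may fall below 80% at ratio 1.25 where that proportion is 40% or less.
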